## Abstract

**Background:**

In low-resource countries such as Ethiopia, the utilization of local data for planning and decision-making health systems was frequently constrained. In addition, despite several government initiatives, maternal health services were not completely utilized. On the other hand, efforts to effectively utilize the local data available to improve the utilization level of maternal healthcare services were insufficient, necessitating the need for a different approach.

**Objective:**

This implementation study aims to test and validate the effectiveness of a data-informed platform for health (DIPH) strategies on data use for decision-making and utilization of maternal health services in districts of the Gedeo Zone, southern Ethiopia.

**Methods:**

A two-arm parallel group, type II hybrid, cluster-randomized control trial design has been implemented to conduct the study between 1 September 2022 and 29 February 2024. Six woredas/districts have been assigned to the intervention arm and the other six to the control arm. Baseline and end-line data have been collected from 120 eligible health management staff (from both intervention arm and control arm). In the intervention arm, district health management staff have been given specialized training and continuous technical assistance as a package called the DIPH strategy by embedding it with the district's current decision-making platform such as Performance Review Team meetings. The DIPH strategy has mainly focused on five-step approaches such as situational assessment, stakeholder engagement, defining/setting priorities, planning, and follow-up. Health management staff in the control arm have performed their regular daily activities. The *χ*^2^ and *t*-tests have been used to check the effect of the intervention. In addition, difference-in-differences estimates have been calculated because the change may inherently occur over time. A *P*-value of <0.05 and a 95% confidence interval have been used to declare the significance of the intervention.

**Discussion:**

The findings of this study were supposed to give insights into implementation strategies that improve data use in decision-making and utilization of maternal healthcare services at the woreda level and uncover contextual factors that boost the response of these strategies.

## Introduction

1.

Management and problem-solving capacity at all levels are essential for establishing effective and efficient health systems and expanding access to basic healthcare services in resource-limited settings. Effective decision-making is particularly vital in low-income settings, where scarce resources must be carefully stewarded and efficiently deployed to meet the substantial health needs of the population (1, 2). Effectively and efficiently managing the six components of the health management information system (HMIS), namely, indicators, data sources, data administration, information products, distribution, and usage, is possible (3).

At present, maternal and child health (MCH) care services [antenatal care (ANC) services, delivery, postnatal care (PNC) services, and so forth] are the most prioritized service areas that need critical decisions globally and require special attention to reduce maternal mortality and morbidity to achieve sustainable development goals (SDGs) (4). Therefore, a standardized and widely employed approach or strategy that increases the use of locally available data is needed to improve the performance of those services. As a result, the data-informed platform for health (DIPH) is one of the approaches aimed at improving data use and mother and child health (5).

The DIPH is a straightforward procedure for district-level decision-making based on health data and would aid in addressing local community needs better (5). DIPH is a structured decision-support approach aimed at encouraging the use of locally available data in health decision-making at the district level. With the systematic use of data by district administrative and program leaders for health program prioritization and planning, progress monitoring, and follow-up across various health domains (such as maternal, newborn, and child health), the adoption of the five-step DIPH approach—situational assessment, stakeholder engagement, defining/setting priorities, planning, and follow-up—has simplified the utilization of local-level program management and health service data. A method for including diverse stakeholders in structured health decision-making at the district level is included, which is already in place (5–7).

In low-resource countries such as Ethiopia, the utilization of local data for health system planning and decision-making is frequently constrained (7). The HMIS generates huge amounts of data regarding health service delivery and population health, enabling decentralized health systems to make data-driven decisions. Health facilities are trying to utilize local data available in health sectors (health post, health center, and hospital), such as daily, weekly, monthly, quarterly, and annually reported services and diseases, as well as data from other sectors such as nutrition, water, and sanitation, and other data directly related to the improvement of maternal health services (4). However, the data are rarely used locally (5). In practice, HMIS data are underutilized at the community and district levels because there is no defined process for their utilization, or they may be unavailable, incomplete, or of poor quality (8, 9).

Improving health information systems will initially result in improved outputs of higher quality and timely data. Then, data must be utilized to improve the functioning of the five other building blocks of the health system, namely, health services, the workforce, medical supplies, financing, and leadership to finally affect service delivery and health outcomes. However, data are frequently insufficiently utilized in program creation and improvement, policy formulation, strategic planning, or advocacy and instead sit on reports, shelves, or databases (8).

According to the literature, the overall level of routine data or health information used for decision-making among health workers working in health institutions is insufficient and varies by country and region of the world. In some African countries other than Ethiopia, it runs from 38% in Côte d'Ivoire to 69.6% in Kenya (10–14). The result of a systematic review in Ethiopia revealed that the overall utilization of data among care providers was 57.42% (15), which ranges from 45.8% in the East Gojjam Zone to 78.5% in North Gondar (16–20).

Evidence suggests that if locally available data are not well utilized, decisions to improve the performance of major health services may be distorted, contributing significantly to their low achievement (7, 17, 21). According to global SDGs (4) and the strategic plan of the Ethiopian health sector (22), maternal health services are identified as a prioritized area. Information revolution is among the five transformation agendas, and the utilization level for those services was low. For example, in eastern African countries, the utilization rate of at least four or more antenatal healthcare services stood at 52.4%, of which 31.82% is from Ethiopia (23). The Ethiopia Mini-Demographic and Health Survey–2019 (EMDHS-2019) shows 74% and 43% of mothers used first and fourth ANC services, respectively. Regarding delivery, 50% were attended by a qualified practitioner, and 48% occurred at a healthcare facility. Moreover, 34% of women received a PNC check-up within the first 2 days after birth, and 41% used modern methods of family planning (FP) (24).

Many factors contributed to the low level of data utilization and performance of maternal healthcare services, including organizational and external factors and a lack of a well-established approach. Evidence is provided for a limited number of procedures, including using locally available data for district-level decision-making. Much has been published about the collection of healthcare data and measures to improve data quality, but how the data are used is less well documented (5, 25).

Standardization and pre-testing strategies in various scenarios would increase the potential of being widely employed. DIPH, which organizes woreda-level decision-making using health data, would help meet the needs of the local community, requiring standardization in our context (5).

Although our country has implemented several plans to enhance health management information systems and maternal and child health services, they have not been achieved as expected (22). Because of this, a structured and well-developed approach, which has the potential to improve the HMIS and MCH services, is very important.

To the knowledge of the researchers, no implementation study in Ethiopia assesses the effects of the DIPH strategy on data use in decision-making and utilization of maternal and child health care services at the woreda level. Therefore, interventional research with a comparison group is necessary to ascertain if the reported benefits are attributable to the evaluation awareness of the personnel of the facility, other secular trends, or impact of the legitimate intervention.

Using the data gathered from this study, managers can establish suitable strategies to address challenges linked to data use and maternal healthcare at the woreda level. Stakeholders such as regional, zonal, and woreda health management staff, program focal persons from each health facility, and other health workers can employ this strategy to improve the utilization of data and maternal health services and scale up to a broader context.

As a result, the current implementation research intends to evaluate the effects of the DIPH strategy on data use in decision-making and utilization of maternal health services in districts in the Gedeo Zone of southern Ethiopia in 2022.

### Outcome

1.1.

•Improved data use in decision-making among health management staff in districts through the DIPH strategy.•Improved utilization level of maternal health services (antenatal care, delivery, postnatal care, and FP services) in districts through the DIPH strategy.

### Research questions

1.2.

•What will be the effect of the DIPH approach on data use in decision-making?•What will be the effect of the DIPH approach on the utilization of maternal health services (ANC, delivery, PNC, and FP)?

## Methods and materials

2.

### Study setting

2.1.

This study has been conducted in Gedeo, one of the administrative zones in the Southern Nations, Nationalities, and Peoples’ Region (SNNPR), Ethiopia. According to the 2007 Ethiopian Population and Housing Census, the total population of the Gedeo Zone was estimated to be 130,433, with an area of 1,210.89 km^2^ (26). Currently, the zone has a total population of 1,086,769 [532,515 (49%) male and 554,224 (51%) female] (27).

The Gedeo Zone has 12 woredas, including Dilla Town, Kochore, Chelelektu Town, Gedeb Town, Chorso, Yirga Chefe Town, Yirga Chefe woreda, Dilla Zuria, Gedeb woreda, Wonago, Bule, and Rappe. It has one referral hospital, three primary hospitals, 38 health centers, 146 health posts, and nine non-governmental organization (NGO) clinics, and there are private health facilities, including low-level clinics, medium clinics, drug stores, and pharmacies that provide health services for the community. Data from the Gedeo Zone health department have estimated the health service coverage to be 92% (28). This implementation study has been conducted in all woredas of the Gedeo Zone by allocating six of them to the intervention arm and six to the non-intervention arm.

### Study design and the implementation period

2.2.

This implementation research has been conducted using a two-arm parallel group, type II hybrid, cluster-randomized control trial (C-RCT) design in the Gedeo Zone woredas. The study has taken 18 months (four cycles with 3–4 months each) including two pre- and post-data collection months (between 1 September 2022 and 29 February 2024). The intervention (DIPH approach) has been provided for district-level management staff as a package, which includes DIPH training, DIPH job aid, and implementation support.

### Study participants

2.3.

The study participants have been the head of the health department, all program officers, and data managers at the woreda level. All eligible woreda staff have been interviewed. We have anticipated that 10 eligible staff members will be available in each woreda, and we have intended to include all of them in the study.

### Eligibility

2.4.

#### Inclusion criteria

2.4.1.

All woredas of the Gedeo Zone and all managerial and administrative staff working in those facilities between 1 and 30 September 2021, pre-intervention, and 1–29 February 2024, post-intervention, have been included in the study. The interventions have been provided from 1 October 2022 to 30 January 2024.

#### Exclusion criteria

2.4.2.

Study participants who have not given consent and those who have worked in their respective woreda for less than 6 months have been excluded.

### Determination of sample size

2.5.

The sample size estimation for the required number of woredas per study arm is based on the statistical formula recommended by Hayes and Bennett (29), assuming 80% power and at least 25 percentage point difference in the performance of data use and maternal healthcare services.$$c=1+(z_{\alpha /2}+z_{\beta }{)}^{2}\frac{\pi_{0}(1-\pi_{0})/m+\pi_{1}(1-\pi_{1})/m+(k_{0}^{2}\pi_{0}^{2}+k_{1}^{2}\pi_{1}^{2})}{{\left(\pi_{0}-\pi_{1}\right)}^{2}}$$where *C* is the number of clusters required (woredas), *Z_α_*_/2_ is the confidence level (95%), Z*_β_* is required power (80%), π_0_ is the true proportion in the absence of intervention (50%), π_1_ is the true proportion in the presence of intervention (75%), *m* implies the individuals sampled in each cluster/woreda (10), *k*_0_ is the coefficient–variation of true proportion in the absence of intervention (0.096942), and *k*_1_ is the coefficient–variation of true proportion in the presence of intervention (0.096942).

**Table d95e524:** 

Indicator	Expected level at baseline	Expected minimum percentage increase	Health management staff assessed/woreda	Number of woredas in study arm
Level of data use in decision-making at the woreda level	50%	25%	10	6
Maternal health service utilization	50%	25%	10	6

Based on the calculations above, a minimum sample size of 120 health management staff (60 per study arm) has been required to conduct the study.

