### Selection of the population and allocation of the intervention

2.6.

The implementation research has been conducted in all woredas of the Gedeo Zone. Study woredas have been treated as clusters, with an equal number allocated to both intervention and non-intervention arms. Matched peer random allocation has been employed. To reduce subjective allocation, matching has been performed based on the performance level of the woredas (based on key indicators) and distance. The woredas have also been classified as urban and rural areas, and six intervention and six comparison arm woredas have been randomly selected in collaboration with the zonal health department. To avoid information contamination between the intervention and control arms, a buffer zone has been created based on the distance within the districts. Finally, all health management staff have been included in the selected woredas (Figure 1).

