### Data management

2.12.

The data already collected have been routinely checked for completeness and consistency. After appropriate cleaning and coding, the data have been entered into EpiData version 4.6 and exported to SPSS version 23 software for analysis. Descriptive statistics have been generated and presented in narrative, figurative, and tabular forms. The *χ*^2^ and *t*-tests have been used in checking the statistical significance of the intervention and the difference in data use in decision-making and utilization of maternal healthcare services within and between groups. We have employed difference-in-differences estimates because the change may inherently happen over time. Therefore, a control group has captured this intrinsic temporal change without DIPH intervention and subtracted it from the change brought by the DIPH intervention to assess the net effect on key study outcomes. We have calculated the absolute differences in percentages from the baseline and the end line, then calculated the net effect by subtracting the absolute DIPH intervention difference from the control. A *P*-value of <0.05 and 95% confidence interval (CI) have been used to declare the significance of the intervention.

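### The printed sample-size formula with its printed inputs gives 8 woredas per arm, not 6; with 6 per arm it implies about 69% power rather than 80%

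*Protocol article*

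**What the plan says.** Section 2.5 (Determination of sample size) states: "The sample size estimation for the required number of woredas per study arm is based on the statistical formula recommended by Hayes and Bennett", "assuming 80% power and at least 25 percentage point difference in the performance of data use and maternal healthcare services". It prints the formula with a leading 1 and defines each term. The normal quantile for α/2 "is the confidence level (95"%), π0 "is the true proportion in the absence of intervention (50"%) and π1 "is the true proportion in the presence of intervention (75"%). The number sampled per woreda is 10, and both coefficients of variation are 0.096942.

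The table that follows lists 6 woredas per arm for each of two indicators, data use and maternal service utilisation. The sentence below it refers back to those calculations and says that "a minimum sample size of 120 health management staff (60 per study arm) has been required".

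Three other sections bear on the point:
- Section 2.1 says the zone has 12 woredas and that all were allocated, six to each arm.
- Section 2.6 says: "Matched peer random allocation has been employed".
- Section 2.12 (Data management) names χ² tests, t-tests and difference-in-differences, and says that a P-"value of <0.05 and 95% confidence interval (CI) have been used to declare the significance of the intervention".

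**The concern.** The article gives the formula, every input and the answer, and the answer does not follow. The shortfall is 2 woredas per arm, or 40 staff in total, and it goes in the favourable direction: the claimed 80% power is not what the calculation delivers at the size used. By the same formula, the chance of missing a true 25-point effect is about 31% rather than 20%. Section 2.14 makes scale-up depend on effectiveness being shown. A reader who trusts the 80% would give a non-significant result more weight as evidence of no effect than the design allows.

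**Working it through.** **Inputs, all from section 2.5.** π0 = 0.50; π1 = 0.75; m = 10; k0 = k1 = 0.096942; two-sided 5% (z = 1.960); 80% power (z = 0.842). The squared sum of the two quantiles is 7.849.

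**Attempt to reproduce the stated 6.** The printed formula is

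c = 1 + (zα/2 + zβ)² × [π0(1−π0)/m + π1(1−π1)/m + k0²π0² + k1²π1²] / (π0−π1)²

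- Sampling terms: 0.25/10 + 0.1875/10 = 0.025 + 0.01875 = 0.04375
- Between-woreda term: 0.096942² × (0.25 + 0.5625) = 0.0093978 × 0.8125 = 0.007636
- Sum: 0.051386
- Squared difference: 0.25² = 0.0625
- c = 1 + 7.849 × 0.051386 / 0.0625 = 1 + 6.453 = **7.45**

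This rounds up to 8 woredas per arm: 80 staff per arm and 160 in total, against the stated 6, 60 and 120. The stated figure is not reproduced. Using z values of 1.96 and 0.84 also gives 7.45.

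**Variants that might explain 6.**

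| Change to the stated inputs | c | Rounded up |
|---|---|---|
| k0 = k1 = 0 | 6.49 | 7 |
| Leading 1 dropped | 6.45 | 7 |
| One-sided 5% | 6.08 | 7 |
| Leading 1 dropped and k = 0 | 5.49 | 6 |

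No value of k alone brings the printed formula to 6. Of the four variants, only the last rounds up to 6, and it both alters the printed formula and discards the stated between-woreda variation.

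**Power at 6 per arm.** Inverting the formula:

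Power = Φ(√[(c−1)(π0−π1)² / 0.051386] − 1.96)

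- c = 6: √(5 × 0.0625 / 0.051386) = 2.466, and Φ(0.506) = **69.4%**
- Cross-check by noncentral t, 10 df: 68.3%
- c = 7: 77.1%
- c = 8: 83.1%

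**Difference detectable with 80% power at 6 per arm.** Keep π0 = 0.50 and try π1 = 0.78. The sum becomes 0.025 + 0.01716 + 0.0093978 × (0.25 + 0.6084) = 0.05023. Then √(5 × 0.28² / 0.05023) = 2.794 and Φ(0.834) = 79.8%. The detectable difference is therefore about **28 points**.

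**If the analysis keeps the pairs.** The matched form replaces the leading 1 by 2, with k read as the within-pair variation. The article gives no within-pair value, so the two ends of the range are shown for 6 pairs:
- matching removes no between-woreda variance (k = 0.096942): √(4 × 0.0625 / 0.051386) = 2.206, power 59.7% (58.5% by paired t, 5 df)
- matching removes all of it (k = 0): √(4 × 0.0625 / 0.04375) = 2.390, power 66.7% (65.2% by paired t, 5 df)

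**The case against.** The best defence is practical. The zone has 12 woredas, all are in the study, and 6 per arm is the most it can supply; asking for 8 per arm is asking for something that does not exist there. That is true, and it decides the remedy. It does not rescue the statement, because the article presents 6 and 120 as what the formula requires, not as what was available.

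A second objection is that 69% is not the power of the trial. This stands in part. The formula compares two proportions at one time point, whereas section 2.12 also plans difference-in-differences. The 69% is what the article's own formula implies at the size used, and should be described that way. Nor can it be carried to the second row of the table. Section 2.9 defines maternal service utilisation as a provider-reported percentage over 10 indicators, not as a yes/no answer from each staff member, so binomial sampling with 10 per woreda does not describe it.

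Three stronger readings are tempting and are not supported:
- A reader might infer from section 2.6 that power is simply 60% because allocation was matched. Section 2.12 does not say that pairs are kept in the analysis, and matching on performance and distance is meant to remove between-woreda variance. Only the conditional range holds.
- A reader might infer that excluding staff with under 6 months' service lowers power further. Section 2.3 anticipates 10 *eligible* staff per woreda, so that exclusion is already accounted for.
- A reader might infer that 60 per arm came from a calculation that ignored clustering. The article does not show its origin; 60 is also just 6 × 10, and 6 is half of 12.

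**Conclusion.** The point holds as an error of arithmetic. The printed formula and inputs require 8 woredas per arm, and at 6 per arm they imply about 69% power, with about 28 points detectable at 80% power. This rests only on figures printed in section 2.5, taken at face value, including the stated coefficient of variation. It applies to the data-use proportion. The pair-preserving range of about 60% to 67% carries the further assumption that the analysis retains the pairs; both ends lie below 80%. No redaction or missing text accounts for the discrepancy, since formula, inputs and result are all given.

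**What to change.** In section 2.5 and its table, stop describing 6 woredas per arm and 120 staff as the minimum that the formula requires. Say instead that the study includes all 12 woredas of the zone, and state what that size gives. Suggested wording:

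*All 12 woredas of the zone are included. For data use in decision-making, 6 woredas per arm with 10 staff each give about 69% power to detect 50% versus 75% by the stated formula (two-sided 5%, coefficient of variation 0.096942). The difference detectable with 80% power is about 28 percentage points. If the analysis retains the matched pairs, power is about 60% if matching removes no between-woreda variance and about 67% if it removes all of it.*

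Remove the maternal service utilisation row from this calculation, because the binomial formula with 10 staff per woreda does not fit that outcome as defined in section 2.9.

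The cost is text only: no change to woredas, staff or data collection. The price is a less favourable power statement.
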